## Discussion

Our study evaluates the implementation and effects of a novel, multidimensional ET feedback and contributes to quality assurance in medical rehabilitation with regard to the process and outcome quality dimensions.

Several operational challenges have to be taken into account during the execution of this study. First, the COVID-19 pandemic might influence the recruitment of study participants. Although the length of the recruitment period was based on the number of eligible patients taking part in the clinic’s rehabilitation program in 2019, 2020 and 2021, COVID-19 might impede patient participation and lead to unexpected dropouts. Therefore, the recruitment period might have to be extended in order to achieve the target sample size. Secondly, the content of the intervention might be influenced by the personal characteristics and social-communicative abilities of the respective exercise therapist performing the ET feedback. Therefore, therapists are required to adhere to the structure and content of the partially standardized ET feedback curriculum. In addition, only two exercise therapists are responsible for the intervention and control group, respectively, thereby minimizing ET feedback variability.

There are several strengths in the design of this study. We expect that the combination of quantitative and qualitative data collection will not only identify the potential effects of multidimensional ET feedback (outcome quality), but also highlight possible difficulties and shortcomings during the implementation of the intervention (process quality). Furthermore, the 12-week follow-up will provide data on the medium-term effectiveness of ET feedback following medical rehabilitation. Finally, the wide spectrum of instruments measuring treatment outcome, patient satisfaction, self-regulation and work ability will allow for the examination of factors influencing participation as described by the ICF model.

Since the clinic’s exercise therapists are responsible for delivering the intervention, this study is limited to a single-blind design. Although both the intervention and control group are organized as closed groups, participant blinding might theoretically be compromised through communication between groups during mealtime or recreational activities. Furthermore, the study-specific information provided to patients during the welcoming event might cause a selection bias and necessitate additional participant recruitment. Finally, due to clinic-specific operational procedures, patient randomization and group allocation has to be performed several days prior to participant recruitment during the welcoming event.

Based on the results of the planned study, multidimensional ET feedback implementations for further indications and rehabilitation clinics might be developed.

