### Setting and participants

Participants are recruited from an inpatient rehabilitation clinic in North Rhine-Westphalia, Germany. To be eligible to participate in this study, patients are required to be at least 18 years old and to meet the following criteria: (1) suffering from neck, shoulder and/or lumbar spine disorders over a period of more than three months, (2) scheduled participation in the inpatient orthopedic rehabilitation program and (3) sufficient knowledge of the German language. Exclusion criteria are: (1) acute herniated discs, (2) postoperative conditions following neck, shoulder and/or lumbar spine surgery less than two months ago, or (3) language barriers. The eligibility criteria for the therapists performing the intervention are: (1) an ET-related qualification (e.g. certified sports scientist or physical therapist) and (2) a minimum of three-year experience with group ET treatments (e.g. back schools, aquatic therapy or medical nordic walking). The patients are informed by the clinic staff about the study’s content, design and eligibility criteria during the welcoming event at the start of the rehabilitation program. Individuals who are interested in participating are required to provide written informed consent. The participants receive no financial compensation for their participation in the study. The coordinating investigator ([name]) randomly assigns the participants to the intervention group or the control group following a 1:1 allocation using blocked randomization. The corresponding block size is independently provided by the funding body refonet and is not disclosed to ensure concealment. The coordinating investigator ([name]) holds the randomization key. All data related to personal information are pseudo-anonymized. Although participants are blinded to the allocation, blinding of the clinic staff is impossible due to the content of the intervention.

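### Patients are allocated several days before recruitment and consent, so the undisclosed block size named in the Methods does not ensure allocation concealment

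*Protocol article*

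**What the plan says.** Under Setting and participants, the Methods give this order. First, "The patients are informed by the clinic staff about the study’s content, design and eligibility criteria during the welcoming event". Next, "Individuals who are interested in participating are required to provide written informed consent". After that, the coordinating investigator "randomly assigns the participants to the intervention group or the control group following a 1:1 allocation using blocked randomization". Concealment is tied to one device: "The corresponding block size is independently provided by the funding body refonet and is not disclosed to ensure concealment". The coordinating investigator also holds the key. The section closes by stating that participants do not know their allocation, whereas "blinding of the clinic staff is impossible due to the content of the intervention".

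The limitations at the end of the Discussion give a different time order: "patient randomization and group allocation has to be performed several days prior to participant recruitment during the welcoming event". The reason given is the clinic's operational procedures. The same paragraph says, as a separate point, that the study information given at the welcoming event "might cause a selection bias and necessitate additional participant recruitment".

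The Statistical analysis section makes the complete-case analysis primary and adds an intention-to-treat analysis for robustness. It names age and gender as covariates and plans a dropout analysis aimed at differential attrition.

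**The concern.** Concealment means that nobody who decides on a patient's entry can know or predict that patient's arm until entry is settled. If the arm is fixed days before information, eligibility and consent, an undisclosed block size gives no protection for that patient. Protection then depends on who can see the allocation.

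A reader of the Methods alone would take this for a trial that obtains consent and then randomises with concealment. The Discussion shows that it is not. If entry depends on arm, the consenting patients in the two groups are no longer comparable by design. The complete-case analysis and an intention-to-treat analysis of consenters would both inherit the difference. Adjustment for age and gender would remove only the part those two variables explain.

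**Working it through.** **Order of events.** No stated figure decides this point, so the sections are set side by side.

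| Step | Methods, Setting and participants | Discussion, limitations |
|---|---|---|
| Information to patients | Welcoming event, by clinic staff | Welcoming event |
| Written consent | Follows the information | Part of recruitment at that event |
| Random assignment | Described after consent, applied to participants | Several days before that event |
| Basis of concealment | Undisclosed block size | Not discussed |

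1. Recruitment takes place at the welcoming event and allocation comes days earlier. The true order is therefore allocation, information, consent.
2. The block size bears on predicting an assignment not yet drawn. At the welcoming event the assignments of the patients present already exist, so the device does not address the risk that this order creates.
3. The Discussion lists the timing as a limitation but does not connect it to concealment. The selection bias it names is attributed to the study information, not to allocation before consent. The statement in the Methods is left uncorrected.
4. Patient satisfaction is a primary outcome measured only at T1 and T2 (Table 3). With no T0 value, arm-dependent selection on that outcome can be neither checked nor adjusted for directly.

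**Illustration of size.** The decline rates and the gaps between decliners and consenters below are assumptions; the article gives neither. The SD of 2.5, the target of 2.0, the 33 per group and the one-sided 5% level come from the Sample size calculation section.

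Suppose all pre-allocated patients have the same mean in both arms, a share d declines, and decliners differ from consenters by g. The consenter mean is then shifted by d × g. The bias in the group difference is d₁g₁ − d₂g₂.

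- Same d and same g in both arms: bias 0.
- Decline 35% against 20%, gap 1 point in both arms: (0.35 − 0.20) × 1 = 0.15 points.
- Decline 30% in both arms, gap 1 point in one arm only: 0.30 × 1 − 0.30 × 0 = 0.30 points.

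The planned standard error is 2.5 × √(2/33) = 0.615. The largest case is 0.30/2.0 = 15% of the target and 0.30/0.615 = 0.49 standard errors.

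With no true effect and a shift b towards the hypothesis, the one-sided 5% error becomes Φ(b/SE − 1.645). With 66 per arm, SE = 2.5 × √(2/66) = 0.435.

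| Assumed shift b (BPI points) | 33 per arm | 66 per arm |
|---|---|---|
| 0 | 5.0% | 5.0% |
| 0.1 | 6.9% | 7.9% |
| 0.2 | 9.3% | 11.8% |
| 0.3 | 12.4% | 17.0% |
| 0.5 | 20.3% | 31.0% |

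A larger sample does not dilute a bias of this kind; the error rate rises because the standard error shrinks.

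**The case against.** The strongest defence is that the authors disclose the timing and its reason, and that nothing shows selection by arm takes place. Several parts of this stand.

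- **Staff access.** A reader might infer that concealment is absent because the staff at the welcoming event know each patient's arm. The article does not say so. It names only the coordinating investigator as allocating and holding the key. It explains the lack of staff blinding by the content of the intervention, which the clinic's exercise therapists deliver. Access to the list is also a detail that an article may leave to the full protocol.
- **Participant blinding.** Patients are stated not to know their allocation, so they are unlikely to choose by arm. Self-selection that is the same in both arms narrows the population but does not bias the comparison. What remains is staff approach, encouragement, and eligibility items that need judgement, such as sufficient knowledge of German.
- **Additional recruitment.** A reader might take the Discussion to offer more recruitment as a cure for selection bias. The sentence presents selection bias and further recruitment as two possible consequences of informing patients. It claims no remedy.
- **Order in the Methods.** No word there states that assignment follows consent. The impression comes from sentence order and from calling those assigned participants.

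Disclosure in the Discussion does not repair the claim in the Methods. Whoever has access to the list, the undisclosed block size does not do what the article says it does.

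**Conclusion.** The concealment statement is wrong as written, and the two sections must be reconciled. This follows from the article's own account of the timing and needs no assumption. The supported conclusion is that the procedure described does not ensure concealment. The article does not show that concealment failed or that selection differed by arm.

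The size of any bias is unknown. The range of 0 to 0.30 BPI points rests wholly on assumed decline rates and gaps. At its upper end it is small beside the 2.0-point target, yet it would more than double a 5% one-sided error. These figures illustrate what is at risk and are not estimates for this trial.

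**What to change.** 1. **Correct the text.** State the order in the Methods as allocation, information, consent. Withdraw the claim that the undisclosed block size ensures concealment, or limit it to what block size can do.
2. **Withhold the allocation.** For patients still to be recruited, keep it from everyone who judges eligibility, informs patients or takes consent until the form is signed, as far as clinic procedures allow.
3. **Report from allocation onwards.** Count pre-allocated, eligible, consented and declined patients by allocated arm, and start the flow chart there. Compare consent rates and the baseline characteristics of consenters between arms. Note that equal consent rates do not exclude selection: the 0.30-point case above has 30% declining in both arms.
4. **Analysis.** Analyse consenters as allocated, with the T0 value in the model for the BPI and the indication-specific scales. Satisfaction has no T0 value, so this does not help there. State that neither this analysis nor the intention-to-treat analysis is fully protected against selection between allocation and consent.

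The cost is revised wording, a simple log of counts and a change in when the allocation is released. No extra patients are needed. There are two downsides. The stated design quality becomes less favourable. And since recruitment began in July 2022 (Study design), step 2 cannot protect patients already enrolled; for them, only steps 1, 3 and 4 apply, with counts taken from clinic allocation records where these were kept.

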## Data Availability

Not applicable.

## Abbreviations

BPI: Brief Pain Inventory
CSQ-8: Client Satisfaction Questionnaire
DRKS: German Clinical Trial Register
ET: Exercise therapy
ICF: International Classification of Functioning, Disability and Health
NPAD: Neck-Pain and Disability Scale
PROMs: Patient-reported outcome measures
QuickDASH: Shortened Disabilities of the Arm, Shoulder and Hand Questionnaire
RCT: Randomized controlled trial
RMDQ: Roland and Morris Disability Questionnaire
SD: Standard deviation
SPIRIT: Standard Protocol Items—Recommendations for Interventional Trials
WAS: Work Ability Score
ZUF-8: Questionnaire to Evaluate Patient Satisfaction
